### Monitoring protocols

#### Development of the protocols

All gynaecologists of the participating centres were approached and they participated in a consensus process, during which the final protocols were designed. Nearly all were obstetricians specialised in hypertensive disorders of pregnancy. After reaching consensus, the protocols were distributed among all providers of care in the study.

#### The protocols

Figure 2 shows the process of recurrence risk guided care.

**Figure 2 F2:**
[figure not shown]
**Recurrence risk guided care (phase 2)**.

#### Regular monitoring

Women will visit the outpatient clinic 9 - 11 times: (8, 12), 16, 20, 24, 28, 32, 36, 38, 39 and 40 weeks gestational age. The visits at 16 and 20 weeks will be scheduled after the first trimester screening procedure and the routine ultrasound screening for structural malformations, respectively. If feasible, six of these eleven visits (12, 20, 28, 36, 39, 40) ought to be performed by the same obstetrician, whereas the remaining five (reassuring) visits (8, 16, 24, 32, 38) may be performed by a nurse-practitioner or may be performed by the gynaecologist of the referring clinic (as of 32 weeks, in regular and intensive monitoring).

#### Intensive monitoring

Women will visit the outpatient clinic 14 - 16 times: (8, 12), 16, 18, 20, 22, 24, 26, 28, 30, 32, 34, 36, 38, 39 and 40 weeks gestational age.

At two occasions during an intensive monitoring pregnancy (16 and 20 weeks), the patient will undergo a series of diagnostic tests, which consist of

1. Measurements in urine: (micro)albuminuria, creatinine, protein (protein serves to calculate the protein-to-creatinine ratio)

2. Measurements in blood: Haemoglobin, platelet count, mean platelet volume, creatinine, urate, CRP, glucose, fibronectin, Flt-1, endoglin

3. 24 h blood pressure monitoring. This assessment is optional (not obligatory)

4. Assessment of the Doppler flow velocity profile in both uterine arteries (at 20 weeks)

Activities other than, or additional to those described in the regular monitoring and intensive monitoring protocols (such as intercurrent admissions, additional outpatient visits or diagnostic testing, or telephone/e-mail contacts) will be registered.

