## Methods/design

### Design

The PreCare study uses a before-after design, in which outcomes and costs before the introduction of the prediction model (i.e. care as usual) are compared with outcomes and costs after introduction of the prediction model (i.e. recurrence risk guided care).

This study consists of two consecutive phases. In the first phase of the study, 50 women receiving care as usual will be followed prospectively from their first pregnancy-related outpatient visit until 3 months post partum. These 50 women will receive questionnaires in order to measure quality of life, anxiety, depression, posttraumatic stress and costs outside the hospital. Retrospective data of an additional group of 200 women who have been treated with care as usual in the past will be collected later on. Then the prediction rule will be introduced. In the second phase, 250 women will receive either protocolised regular monitoring or protocolised intensive monitoring depending on their risk of developing early-onset preeclampsia or HELLP syndrome during their current pregnancy, as estimated on the basis of the prediction model. In regular monitoring, pregnant women are monitored less intensively than in intensive monitoring. Regular monitoring and intensive monitoring are described in detail in the 'Monitoring protocols' section. Figure 1 summarises the design.

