### Recruitment procedures

For the prospective assessment, 50 care as usual patients and 250 recurrence risk guided patients will be included in the study.

The research nurse or the gynaecologist of participating hospitals identifies eligible women by screening the appointment system of the outpatient clinic. After the pregnant woman has given informed consent for participation in the study, patients in phase 1 will be enrolled in care as usual whereas patients in phase 2 will be enrolled in recurrence risk guided care.

In recurrence risk guided care (phase 2), a simple web based risk calculator for the determination of recurrence risk and required intensity of surveillance has been developed and has been made accessible to gynaecologists and research nurses.

Information about the recommended components of intensive monitoring and regular monitoring has been provided together with the risk calculator.

For the retrospective assessment, 200 patients who were treated according to care as usual will be used as a comparator group based on matching. Matching criteria will at least include maternal age (difference < 5 years) and gestational age at delivery. Consequently, at study completion, there will be 250 care as usual patients who will be compared with 250 recurrence risk guided patients.

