### Data collection

For the prospective assessment (n = 50 care as usual; n = 250 recurrence risk guided care), baseline demographics, past obstetric and medical history will be recorded in case report forms. Information is obtained on the condition of mother and child, infant weight, infant length, morbidity and mortality from the infant and maternal records. If applicable, details of the admittance of the child to the neonatal intensive care, high care or medium care unit will also be collected. All activities in the hospital will be documented until three months postpartum.

We will assess not only clinical outcomes, but also health-related quality of life by using the EQ-5 D [19], anxiety by using the STAI [20], depression by using the Beck Depression Inventory [21] and posttraumatic stress by using the PTSD Symptom Scale [22]. The QoL questionnaires will be administered at 3-month intervals between baseline (before 20 weeks of pregnancy), at 29 weeks of pregnancy, ten days and three months postpartum. Costs outside the hospital, such as GP care, midwife and maternity care, productivity losses and out-of-pocket expenses will be obtained by means of a retrospective cost questionnaire with a recall period of 3 months. Long-term follow up of the women and children may be possible, but is not included in the current study.

For women enrolled in the retrospective assessment (n = 200), all data described above will be collected, except data on health-related quality of life, anxiety, depression, posttraumatic stress and costs outside the hospital.

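### Hospital resource use is captured prospectively for all 250 guided-care women but for only 50 of 250 usual-care women, so the hospital-cost difference may partly reflect how the data were recorded

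*Protocol article*

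**What the plan says.** The Design section sets up two kinds of usual-care data. First, "50 women receiving care as usual will be followed prospectively from their first pregnancy-related outpatient visit until 3 months post partum". Second, "Retrospective data of an additional group of 200 women who have been treated with care as usual in the past will be collected later on". Recruitment procedures then pools them: at completion "there will be 250 care as usual patients who will be compared with 250 recurrence risk guided patients".

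Data collection describes the prospective part: "For the prospective assessment (n = 50 care as usual; n = 250 recurrence risk guided care), baseline demographics, past obstetric and medical history will be recorded" on case report forms. Clinical information, including "morbidity and mortality from the infant and maternal records", is taken from the charts. For hospital resource use, "All activities in the hospital will be documented until three months postpartum". For the rest of the comparator, "For women enrolled in the retrospective assessment (n = 200), all data described above will be collected, except data on health-related quality of life", the psychological scales and costs outside the hospital. The retrospective women are thus meant to supply the same in-hospital items as the prospective ones.

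The end of the Intensive monitoring section adds a further layer. Anything other than, or additional to, what the regular and intensive protocols prescribe ("such as intercurrent admissions, additional outpatient visits or diagnostic testing, or telephone/e-mail contacts) will be registered") is recorded. Those two protocols apply only in phase 2.

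The Data analysis section names adjustment for potential confounders and a multilevel analysis for hospital. The Economic evaluation section plans a decision model, partly because some usual-care parameters are missing.

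**The concern.** Capture differs by group. Every guided-care woman is observed while a study record is being kept, with explicit registration of extra contacts. Four in five usual-care women were treated before anyone was recording for the study. The items most exposed are those that routine care has least reason to document fully: telephone and e-mail contacts, and to a lesser degree unscheduled visits and extra tests.

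Cost-effectiveness is the first stated aim, and the Discussion expects mean cost per patient to fall because surveillance becomes less intensive. If usual-care activity is under-recorded, usual care looks cheaper than it was and the saving is understated. A worthwhile strategy could then be judged not worthwhile.

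This is a measurement problem, distinct from change over time. It would remain if the 200 retrospective women were recent and matched on hospital.

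**Working it through.** **Inputs from the protocol article**

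- Guided care, prospective: 250 (Recruitment procedures; Data collection).
- Usual care, prospective: 50 (Design).
- Usual care, retrospective: 200 (Design).
- Completeness of the retrospective records: not given. Write it as *s*, the fraction of an item that these records hold relative to prospective registration. All values of *s* below are assumptions.

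**Step 1. The plan's own counts.** 50 + 200 = 250 usual-care women, against 250 in guided care. The stated 250 v 250 is reproduced.

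**Step 2. Share captured prospectively.** Guided care: 250/250 = 100%. Usual care: 50/250 = 20%, leaving 200/250 = 80% retrospective.

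**Step 3. Effect on a pooled usual-care total.** Taking capture as complete in the 50 and *s* in the 200:

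recorded fraction = (50 × 1 + 200 × *s*)/250 = 0.2 + 0.8*s*

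understatement = 1 − (0.2 + 0.8*s*) = 0.8(1 − *s*)

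| *s* (assumed) | Recorded fraction | Understatement | Guided/usual ratio if there is no true difference |
|---|---|---|---|
| 1.00 | 1.00 | 0% | 1.00 |
| 0.95 | 0.96 | 4% | 1/0.96 = 1.04 |
| 0.90 | 0.92 | 8% | 1/0.92 = 1.09 |
| 0.80 | 0.84 | 16% | 1/0.84 = 1.19 |

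These figures apply item by item, not to total cost. On an item where *s* = 0.90, a true saving of 8% of the usual-care total would be cancelled exactly, since 0.8 × 0.10 = 0.08.

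**Step 4. Does a planned analysis remove it?** Adjustment for confounders deals with differences between the women, and the multilevel analysis with clustering by hospital. Neither restores contacts that were never written down in one group. The decision model is justified by parameters that are absent; a parameter that is present but under-counted would enter it as it stands.

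**Step 5. Which outcomes are exposed?**

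- *Primary outcome.* It requires delivery before 34 weeks (Study outcomes), which routine records should hold. Clinical outcomes of the prospective women come from medical records too. Little exposure.
- *Caesarean section, NICU admission, gestational age at delivery, mortality.* The same reasoning applies. Little exposure.
- *Gestational age at onset of preeclampsia.* This depends on when signs were looked for and noted. Some exposure.
- *Hospital resource use, especially minor and unscheduled contacts.* Exposed as in Step 3.

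**The case against.** The strongest reply is that under-recording is inferred. The article does not say what the 200 women's data are extracted from. Visits, admissions and tests might come from hospital administrative systems in both periods, in which case *s* would be close to 1 for the main cost items. A condensed article may properly leave the extraction form to the full protocol. This stands in part: the bias is a risk and could be zero.

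Second, the article does not say that the register of extra activities feeds the cost comparison. Protocol adherence is a secondary outcome, and the examples given for hospital costs are outpatient visits and admissions. That is fair, but the Economic evaluation section counts all hospital resource use, and additional visits and intercurrent admissions are among the registered activities.

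Third, the bias runs against guided care, so it cannot manufacture a saving. This is right and limits the seriousness, but an understated saving is still a wrong answer to the main economic question.

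Fourth, a sensitivity analysis by data source is ordinary SAP content. That holds for the reporting step. It does not hold for the choice of source, which has to be settled while data are being collected, and the article itself fixes the pooled comparison.

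**Conclusion.** The point holds for the hospital-cost comparison as a risk of differential measurement of unknown size. The certain part is the asymmetry: 100% prospective capture against 20%. The conditional part is an understatement of 0.8(1 − *s*) on each affected usual-care item: 4%, 8% or 16% at assumed completeness of 95%, 90% or 80%, and nothing if the records are complete. The calculation also assumes full capture in the 50 prospective usual-care women.

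A reader might infer two stronger conclusions that the article does not support.

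- *That the recurrence and morbidity comparisons are biased in the same way.* Clinical outcomes of the prospective women are themselves taken from medical records, the same clinical items are planned for the 200, and the primary outcome is tied to an early delivery. Only softer items, such as gestational age at onset, keep some risk.
- *That a stated share of the saving in visits is lost.* One could set all usual care at 16 visits, put guided care at 0.67 × 11 + 0.33 × 16 = 12.65, and show the saving of 3.35 falling to 16 × 0.92 − 12.65 = 2.07 at 90% completeness. That applies the loss to booked visits, which are the least likely to go unrecorded. It also places all usual care at the top of the intensive schedule, although the section on the health care problem says that care ranges from regular to intensive surveillance. And visits are not costs.

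**What to change.** 1. Base the 250 v 250 hospital-cost comparison on items extracted from the same source in both periods, and name that source.
2. For actively registered items (telephone and e-mail contacts and the like), take the usual-care value from the 50 prospective women only, provided these items are registered for them in the same way. Otherwise leave the items out of the main comparison.
3. Report the hospital-cost difference for the 50 prospective usual-care women v the 250 guided-care women as a sensitivity analysis beside the pooled result.
4. Optionally, apply the retrospective extraction form to those 50 women and compare it with their case report forms. This estimates *s* directly and replaces the assumed values above.

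The cost is small: slightly fewer cost items in the main comparison, a less precise 50 v 250 estimate and, if step 4 is taken, a second chart extraction for 50 women. Group sizes and the primary analysis do not change.

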#### Study outcomes

Recurrence risk guided care will be compared with care as usual with respect to several outcomes.

Primary outcome is the occurrence of either early-onset preeclampsia or HELLP syndrome. Early-onset preeclampsia and early-onset HELLP syndrome are defined according to the criteria of the International Society for the Study of Hypertension in Pregnancy with the criterion of delivery before 34 weeks after the last menstrual period [23]. Secondary clinical outcome measures are: gestational age of onset of preeclampsia, eclampsia, HELLP syndrome, intrauterine growth restriction, caesarean section, admission to the neonatal intensive care unit (NICU), gestational age at delivery and maternal/infant mortality. Other secondary outcome measures are societal costs, quality of life, anxiety, depression, development of posttraumatic stress, satisfaction with treatment, protocol adherence and cost-effectiveness.

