### The health care problem

Although preeclampsia and HELLP syndrome are considered diseases of the first pregnancy, the risk of developing recurrent preeclampsia or HELLP syndrome is increased among parous women with preeclampsia and/or HELLP syndrome in their previous pregnancy. Sep et al. [16] conducted a literature search in order to identify prediction tests for recurrent disease. The recurrence rates reported vary from none to 31 percent for preeclampsia and from 3 percent to 7 percent for HELLP syndrome. Fortunately, the majority of women with a history of preeclampsia or HELLP syndrome have uncomplicated subsequent pregnancies.

To the best of our knowledge there is at this moment no consensus about the management of pregnant women with a history of early-onset preeclampsia or HELLP syndrome.

As a result, follow-up and counselling of these patients varies per centre, gynaecologist and patient, and is largely based on the perceived risk by the responsible care provider of recurrence of the disease in the next pregnancy and the level of anxiety of the patient and its resulting demand for care. Formerly preeclamptic patients are often subjected to various medical screening programmes to detect associated disorders, followed by additional exams by other specialists or the initiation of some management (postpartum evaluation). During a next pregnancy, care varies from regular surveillance by the gynaecologist to intensive surveillance and counselling in order to identify the onset of adverse pregnancy course as early as possible.

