### Statistical analysis

#### Sample size

Sample size calculation was based on the expected fraction of women assigned to regular monitoring either on the basis of the prediction rule or gestational age at the time of previous delivery (67%), the expected failure rate within this category (2%), a type I error (one-sided) of 0.05 and a type II error of 0.2. In order to be able to exclude failure rates of 5% or more, 150 patients assigned to regular monitoring are needed. This means that results of about 225 patients in the recurrence risk based care are needed. The estimated number of 250 allows for drop out and incomplete data of 25 patients.

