As the care provided to women assigned to regular monitoring is less intense, a possible consequence may be that the detection of clinical signs of preeclampsia or HELLP syndrome is somewhat later than in the current care as usual approach. However, we do not expect this to lead to adverse maternal or fetal outcomes, because the prediction model suggests that the recurrence rate in this group is low (< 1%) whereas there is also increased alertness for early signs of pregnancy complications in women with a history of preeclampsia or HELLP syndrome.

In summary, the PreCare study is designed to provide information on whether recurrence risk guided care is a worthwhile strategy compared to current care for pregnant women who suffered from preeclampsia or HELLP syndrome during their previous pregnancy.

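### The primary outcome depends on delivery before 34 weeks, so the later detection foreseen under regular monitoring can move cases out of the count, with unknown size and direction

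*Protocol article*

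**What the plan says.** All references are to the Protocol article.

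- **Study outcomes** makes early-onset preeclampsia or HELLP syndrome the primary outcome, defined "with the criterion of delivery before 34 weeks after the last menstrual period". Age at onset, eclampsia, HELLP syndrome, growth restriction, NICU admission, age at delivery and maternal or infant mortality are among the secondary outcomes.
- **Regular monitoring** schedules visits, apart from the optional early ones, at "16, 20, 24, 28, 32, 36, 38, 39 and 40 weeks gestational age".
- **Intensive monitoring** schedules them at "16, 18, 20, 22, 24, 26, 28, 30, 32, 34, 36, 38, 39 and 40 weeks gestational age".
- **The health care problem** describes the comparator only in general terms: in a next pregnancy, "care varies from regular surveillance by the gynaecologist to intensive surveillance and counselling". No visit schedule is given for care as usual.
- **Sample size** aims to rule out a failure rate of 5% or above in 150 women on regular monitoring, and plans on "the expected failure rate within this category (2" (that is, 2%).
- **Data analysis** makes the incidence of the same outcome, in recurrence risk guided care versus care as usual, the primary analysis.
- **Discussion** accepts as a possible consequence of regular monitoring that "the detection of clinical signs of preeclampsia or HELLP syndrome is somewhat later than in the current care as usual approach". It expects no adverse outcomes from this, partly because "the prediction model suggests that the recurrence rate in this group is low (< 1" (that is, below 1%).

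**The concern.** Seeing women less often does not cause preeclampsia, but it can change when the disease is recognised. The protocol itself names later recognition as the possible cost of regular monitoring. The primary outcome, however, needs two things: the disease, and a delivery before 34 weeks. The second is partly a clinical decision taken after the disease is found. A woman whose disease begins before 34 weeks, is found late and is delivered at or after 34 weeks is therefore a non-failure.

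The outcome can thus be influenced by the intervention through a route other than the one of interest. Both the 5% limit and the primary comparison rest on it. A reassuring result could partly reflect cases that slipped past the cut-off rather than women who stayed well, and the primary outcome alone could not tell the two apart.

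**Working it through.** **1. Where the schedules differ before the cut-off.** From 16 weeks, visits before 34 weeks are:

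- regular: 16, 20, 24, 28, 32
- intensive: 16, 18, 20, 22, 24, 26, 28, 30, 32

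The difference is the visits at 18, 22, 26 and 30 weeks. After 32 weeks, the next regular visit is at 36 and the next intensive visit is at 34, which is already at the cut-off. Neither protocol has a visit after 32 and before 34 weeks. The 32-36 week gap therefore does not separate the two protocols on this outcome. It might matter against care as usual, but that schedule is not given.

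**2. How many events carry the conclusion.** Inputs from Sample size: n = 150, expected rate 2%, limit 5%, one-sided alpha 0.05.

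- Expected failures: 150 × 0.02 = 3.
- Exact binomial rule: P(X ≤ 2 | 150, 0.05) = 0.018 and P(X ≤ 3 | 150, 0.05) = 0.055. The second exceeds 0.05, so 5% is excluded only with 2 or fewer failures.
- Wald upper limit, x/n + 1.645 × √[(x/n)(1 − x/n)/n]: 4.8% for x = 4 and 5.7% for x = 5, so 4 or fewer.

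The plan does not say which rule applies. Under either, one case moved across 34 weeks at the boundary reverses the conclusion.

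On the plan's own figure: the Wald formula with the variance at 2% gives (1.645 + 0.842)² × 0.02 × 0.98 / 0.03² ≈ 135, and an exact calculation gives 234. I could not reproduce 150. That is a separate matter, and nothing here rests on it. The later steps do reproduce: 150/0.67 = 224 (stated as about 225), and 225 + 25 = 250.

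**3. Illustration of a shift past 34 weeks.** Let p = 5% be the rate that would be counted if detection were not delayed, and s the share of those cases whose delivery moves to 34 weeks or later. The documents give no value for s; 10-40% is an assumption. Counted rate r = p(1 − s). Chance of passing = Σ C(150, x) rˣ (1 − r)¹⁵⁰⁻ˣ for x = 0 to 2.

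| s | Cases moved (7.5 × s) | r | P(2 or fewer) |
|---|---|---|---|
| 0 | 0 | 5.0% | 0.018 |
| 10% | 0.75 | 4.5% | 0.033 |
| 20% | 1.5 | 4.0% | 0.058 |
| 30% | 2.25 | 3.5% | 0.101 |
| 40% | 3.0 | 3.0% | 0.169 |

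**4. The opposite direction.** Suppose late-found disease is more advanced and delivered sooner, so that counted failures rise by a quarter, from 2.0% to 2.5% (also an assumption). The chance of 2 or fewer failures then falls from 0.42 to 0.27. The endpoint would then count against regular monitoring.

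**5. The two recurrence rates.** In 150 women, a rate below 1% means fewer than 1.5 failures, and 2% means 3. The reassurance in the Discussion uses a rate less than half the one the design plans on.

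**The case against.** A reader might infer that the 32-36 week gap guarantees later detection under regular monitoring, and that later detection lowers the failure rate and is scored as success. The documents do not support this, and the case against it is strong.

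- The gap is shared up to the cut-off, as step 1 shows, and a case that an intensive visit would have found at 30 weeks can still be seen at the regular visit at 32.
- Symptomatic women may present between visits. The protocol foresees additional visits and admissions and registers them.
- Delivery does not follow detection mechanically. The Background section on the disease describes expectant management of mild disease and prolongation before 34 weeks when mother and fetus are doing well. Late-found disease may also be delivered sooner. The direction is open.
- Care as usual ranges from regular to intensive surveillance, so how much more often those women are seen is unknown.
- The shift shares have no anchor in the documents.
- Several secondary outcomes would record late or severe disease, so the study as a whole is not blind to it.
- Restricting the primary outcome to early-onset disease is a legitimate choice. That later recurrence falls outside it is not an error.

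All of this stands and removes any claim of a known bias. It does not remove the dependence itself: the outcome turns on a delivery date that surveillance can influence, the protocol foresees later detection than in care as usual, and the article ties neither the 5% criterion nor the primary analysis to the secondary outcomes.

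On the two rates, the lower one is described as what the model suggests, while the 2% covers a group that also includes women assigned by gestational age at the previous delivery. That may explain the difference, but the text does not say so.

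**Conclusion.** The point holds in limited form. The primary outcome can be influenced by the intensity of surveillance, and the later detection foreseen for regular monitoring can move cases past 34 weeks, where they count as non-failures. Whether this happens, how often, and whether it outweighs earlier delivery of more advanced disease cannot be settled from the document.

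The sensitivity is real because events are few: about 3 expected, with one or two cases able to change the conclusion. The rise from 0.018 to 0.03-0.17 assumes an undelayed rate of exactly 5%, a 10-40% shift, 150 women and the exact rule; it is an illustration, not an estimate. The document does not support reading the 32-36 week gap as a flaw peculiar to regular monitoring, or late detection as certain to be rewarded.

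This is a cheap and worthwhile improvement, not a fault that invalidates the design. The mismatch between under 1% and 2% is a separate inconsistency that needs reconciling.

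**What to change.** Keep the primary outcome and add the following to the analysis plan.

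1. **Companion safety outcome** that does not depend on delivery date: any preeclampsia or HELLP syndrome at any gestation, eclampsia, or maternal or infant death. Estimate it in the regular-monitoring women, compare it with care as usual using the same confounder-adjusted multilevel analysis, and show its components separately.
2. **Sensitivity analysis** counting disease with recorded onset before 34 weeks, whatever the delivery date. This recovers cases recognised before 34 weeks and delivered later. It cannot recover cases first found after 34 weeks, because onset is recorded when found; the companion outcome is needed for those.
3. **Mode of detection:** for women in the second phase, report whether each case was found at a scheduled or an unscheduled contact. Contacts beyond the protocols are already registered.
4. **Interpretation:** state that the primary result alone does not establish the safety of regular monitoring and will be read alongside the companion outcome.
5. **Reconcile the rates:** explain or align the figure below 1% in the Discussion with the 2% in Sample size.

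The cost is wording and a little analysis. The clinical items are already listed as outcomes, and Data collection omits only questionnaire data and costs outside the hospital for the retrospective women. The downsides are that a safety conclusion becomes slightly harder to reach, and that the companion outcome includes later disease that is not the study's main target. No change to the visit schedule is proposed.
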